## Methods/design

### Study design

ESCALATES is a prospective mixed methods observational comparative study using a range of qualitative and quantitative data collection approaches to accomplish the study aims (see Table 1). The ESCALATES study is informed by the Learning Evaluation approach in that we will analyze clinical relevant outcome measures that do double-duty as performance measures for practices, thereby fostering learning for practices; we collect and analyze real-time quantitative and qualitative data on important contextual factors, and the goal is to foster cross-Cooperative learning from process and outcome data [40]. Table 2 list key elements of the evaluation.

**Table 1 Tab1:** Data Sources

	Description	Level	Source of data	Type of data	Frequency
Cooperative grant proposals	Cooperative’s initial plan for implementation	Cooperative-level	Collected by ESCALATES team with Cooperatives assistance	Qualitative	Pre-grant award
Other documents	Documents Cooperative’s develop (ex: recruitment materials, PF curricula, etc.)	Cooperative-level	Collected by ESCALATES team with Cooperatives assistance	Qualitative	Throughout study period
Online diaries	Online journal; approximately 5-13 people per Cooperative; document implementation experiences	Cooperative-level	Online, interactive communication platform	Qualitative	Post 2x mo.; Start-up to post-implementation
Cooperative site visits	To observe and understand how interventions are implemented	Cooperative-level	Fieldnotes	Qualitative	Annually years 2 and 3
Sustainability site visits	To understand how/which parts of the D&I infrastructure is sustained beyond the life of the grant	Cooperative-level	Fieldnotes	Qualitative	Year 4
Semi-structured interviews	To understand barriers/facilitators of specific aspects of implementation; experience with intervention; mechanisms of change	Cooperative-level	Interviews with Cooperative key stakeholders	Qualitative	Annually with 5-8 people or as needed
Clinical quality measures (ABCS)	Proportion of patients meeting ABCS and data source (e.g. EHR, chart review)	Aggregated by Practice	Medical Record (EHR extraction/chart reviews); collected by Cooperatives; shared with ESCALATES	Quantitative	Baseline through end of study; Quarterly

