### Longitudinal research questions

#### Identifying and distinguishing Cooperatives’ intervention approaches

A central aspect of Cooperatives’ interventions involves developing the infrastructure needed to rapidly deliver external support to approximately 250 practices. The ESCALATES team will analyze qualitative data to characterize the specifics of each Cooperative’s external support strategy and to create typologies that distinguish interventions and characterize the infrastructure Cooperatives develop to support practices. Typologies are a system for categorizing Cooperatives and their participating practices into groups based on a set of salient characteristics. Groupings will be quantified and become variables in subsequent quantitative analyses. This mixed methods procedure is to converge the data using data transformation so that a quantitative analysis can be used based on quantifying the qualitative findings. To do this, the ESCALATES team will analyze qualitative data using a grounded theory approach [54–56] to characterize the factors that emerge as barriers/facilitators to implementation (e.g., practice, context/environmental, and intervention characteristics), how and by whom external support is delivered and the factors that affect this, and what changes practices implement and why. We will make comparisons across Cooperatives, paying particular attention to factors leading to a Cooperative excelling or struggling in response to the intervention. We will create matrices to display data for comparative analyses as suggested by Miles and Huberman [57]. As the ESCALATES team develops initial classifications, these will be shared with Cooperatives as a form of “member checking,” a qualitative research verification step accomplished by asking key informants to validate study findings [58–61]. This analytic strategy will result in rich interpretive summaries of each Cooperative’s intervention, particularly with respect to core features of intervention strategies and other characteristics the ESCALATES team identify as important to D&I. Summaries and matrices will lead to the development of a series of typologies that categorize and transform important aspects of the Cooperatives and their interventions into quantitative variables. For example, external support (e.g., practice facilitation, expert consultation), mode of intervention (e.g., face-to-face, email, phone), frequency (number) and duration (length) of contacts might be made into a composite variable to represent intensity of external support for use in subsequent quantitative analyses.

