
#### Effect of intervention strategies on change in outcomes

Examining the effectiveness of external support interventions will involve estimating differences in ABCS and practice capacity outcomes for different intervention strategies received by practices engaged in each Cooperative, as well as differences in practice implementation. Intervention strategies will be compared to each other and/or to a control group of practices using a differences-in-differences (DID) approach [62]. The DID model is a flexible approach which can accommodate different study designs Cooperatives may propose to evaluate their own interventions. Conceptually, cluster-randomized designs, interrupted time studies, and step-wedge designs can be nested within the DID framework. The primary requirements are the inclusion of baseline (pre-intervention) data and data from a control group. In addition to examining the effectiveness of intervention typologies as assigned, we will also conduct sub-analyses that include differing levels of fidelity to quality improving strategies practices use. The DID approach has been frequently used by health services researchers and economists to account for potential secular effects and changing policies that would affect both intervention and control groups over time, while adjusting for potential confounders [7, 63–68].

The overall analysis to assess intervention strategies on ABCS performance can be considered as shown in the equation$$ {\boldsymbol{Y}}_{\boldsymbol{it}}=\boldsymbol{f}\left(\boldsymbol{\alpha} +{\displaystyle \sum_{\boldsymbol{j}=1}^{\boldsymbol{r}}}{\boldsymbol{\beta}}_{\boldsymbol{j}}{\boldsymbol{I}}_{\boldsymbol{j}}+\boldsymbol{\delta} {\boldsymbol{\tau}}_{\boldsymbol{j}}+{\displaystyle \sum_{\boldsymbol{j}=1}^{\boldsymbol{r}}}{\boldsymbol{\theta}}_{\boldsymbol{j}}{\boldsymbol{I}}_{\boldsymbol{j}}{\boldsymbol{\tau}}_{\boldsymbol{j}}\right), $$

where: ***Y***
_***it***_ represents clinic *i’*s performance on an outcome measure (i.e., one of the ABCS measures, mean adaptive reserve score) at time *t*,; ***I***
_***j***_ represents a dummy variable (intervention strategy received variable described above) taking a value of 1 if the clinic was involved in intervention *j* and zero otherwise; and ***τ***

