_***j***_ is a dummy variable taking a value of 1 if the observation took place after the intervention and 0 otherwise, and *f* represents a general function that captures our intent to model performance through a beta regression for ABCS measures and linear regression for practice capacity outcomes. The coefficient ***α*** is an overall intercept representing average baseline performance for all clinics; ***β***
_***j***_ represents the incremental baseline performance differential between clinics in typology *j*, and ***δ*** represents the change in performance pre- and post-intervention, for all clinics. The ***θ***
_***j***_ coefficients are the coefficients of interest, as they capture the relative performance improvement for each group using intervention typology *r*. The qualitative analyses described above will produce *r* variables (e.g., high, medium, low intensity support strategy) (*r* lying somewhere between 3 and 6). In this model, control groups serve as the reference. This equation can be adapted to include additional dummy variables for each time period or a continuous variable to capture linear time trends as well as fixed effects (equivalent to dummy variables) for practices.

The ESCALATES team will use two-way fixed effects models (i.e., a fixed effect for each practice and for each time period) so the results do not rest on some of the stricter assumptions required for random effects models. However, we will also conduct analyses by introducing a practice random intercept and slope to allow intervention effects to vary across practices in the different study arms. This approach explicitly models different clustering levels (e.g. Cooperative, region, practice) [63]. In this case, rather than treating the practice as a nuisance factor, this approach allows each practice to respond differently over time to the intervention and allows the ESCALATES team to estimate those changes and study the heterogeneity of effects due to variation in context across Cooperatives and differences across practices within each Cooperative.

The analyses described above will be conducted for each ABCS measure. In addition, ESCALATES will produce a model that pools all measures and uses measure-specific fixed effects, which will allow for an assessment of an “overall” effect of the interventions.

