This analysis will extend the DID models proposed above by testing individual moderators with a three-way interaction of intervention group, time point and potential moderator. Our choice of variables to include will be based on theory and on triangulation with qualitative findings. Potential moderators include practice characteristics, as significantly associated with ABCS outcomes at baseline, and contextual factors that emerge during implementation. Moderators may be identified through surveys or qualitative data. Moderators identified through qualitative data will be quantified whenever possible. In addition to testing individual moderators, we will consider a composite moderator, which may more strongly moderate the effect of the intervention strategies on ABCS outcomes than any single moderator. Specifically, ESCALATES will create a combined moderator that is developed as a weighted combination of individual selected moderators to identify for which practices different intervention strategies may be preferred. Combining moderators has been shown to exhibit a larger moderator effect size than any individual moderator [67]. We will develop and evaluate a composite moderator using the parametric approach developed by Kraemer [69], which constructs a composite moderator from a weighted average of moderators that are weighted to maximize the correlation between the outcome difference between randomly paired practices and the average of the two values of the moderator variable.

In addition to these quantitative analyses of heterogeneity, we will also conduct qualitative analyses to evaluate the multilevel contextual factors that could affect either the interpretation of the results of each analysis, or that might be useful for others attempting to replicate or reinvent interventions in different times or situations [70, 71]. These analyses will use multiple data sources across multiple levels (from the practice and health care system, the intervention/evaluation team, and the local and national policy context), and will attempt to include diverse stakeholder perspectives of the most important contextual factors at critical points in the project/intervention, to help understand what happened here and why, and what someone else would need to know to transport/re-invent what was learned here in a different time and place. These analyses will enhance the external validity of ESCALATES findings.

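### The composite moderator's weighting rule measures moderation only if the moderators have equal variance in the strategies compared, which this observational comparison does not guarantee

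*Protocol article*

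**What the plan says.** The section *Assessing contextual factors and heterogeneity of intervention effects* has two layers. Individual moderators are examined by "testing individual moderators with a three-way interaction of intervention group, time point and potential moderator". A composite is then formed from selected moderators, with weights chosen by a different rule: they are "weighted to maximize the correlation between the outcome difference between randomly paired practices and the average of the two values of the moderator variable". Its purpose is "to identify for which practices different intervention strategies may be preferred".

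On candidates, the same section says: "Potential moderators include practice characteristics, as significantly associated with ABCS outcomes at baseline". It also names theory, qualitative findings and contextual factors that emerge during implementation as sources.

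On design, *Study design* states: "ESCALATES is a prospective mixed methods observational comparative study". The strategy groups come from qualitative work described under *Identifying and distinguishing Cooperatives' intervention approaches*: "Typologies are a system for categorizing Cooperatives and their participating practices into groups based on a set of salient characteristics". *Effect of intervention strategies on change in outcomes* puts the number of such groups at "lying somewhere between 3 and 6", with control groups as the reference.

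**The concern.** The question is whether a characteristic changes the effect of a strategy. The null is therefore equal slopes of change on that characteristic in the two groups. The pairwise correlation is zero under that null when the characteristic has the same variance in both groups, which randomising practices to strategies would give in expectation. Here groups are assembled from what Cooperatives in different regions delivered. Characteristics such as ownership, rurality or health-system affiliation may be spread quite differently between them.

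Where the variances differ, the rule mixes prognosis with moderation. The composite is meant to guide which practices should get which kind of support. It could point to characteristics that only forecast improvement under any strategy, or pass over ones that do alter the strategy effect.

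**Working it through.** The article gives no figure to reproduce. The check is algebra, followed by assumed values.

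**Set-up.** Draw one practice at random from each of two strategies. Let Y be pre-post change, M the moderator, b1 and b2 the within-group slopes of Y on M, V1 and V2 the within-group variances of M, and s the residual SD. Put D = Y1 − Y2 and A = (M1 + M2)/2.

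**Criterion.**
- Cov(D, A) = (b1·V1 − b2·V2)/2
- Var(D) = b1²·V1 + b2²·V2 + 2s²
- Var(A) = (V1 + V2)/4

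The bracket splits as b1·V1 − b2·V2 = (b1 − b2)·(V1 + V2)/2 + (b1 + b2)/2·(V1 − V2). The first term is moderation. The second is average prognostic slope times variance imbalance, and vanishes only if V1 = V2 or the average slope is zero. With several moderators, equal covariance matrices are needed. Means do not appear, so a difference in means alone is harmless when the outcome is linear in M.

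**Size with no moderation (assumed).** Binary moderator, so V = p(1 − p); b1 = b2 = 5 percentage points of change; s = 10 points; group 2 prevalence 50% (V2 = 0.25).

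| Prevalence | V1 | Cov(D, A) | Var(D) | Var(A) | Correlation |
|---|---|---|---|---|---|
| 10% v 50% | 0.09 | −0.400 | 208.50 | 0.0850 | −0.095 |
| 20% v 50% | 0.16 | −0.225 | 210.25 | 0.1025 | −0.048 |
| 30% v 50% | 0.21 | −0.100 | 211.50 | 0.1150 | −0.020 |
| 50% v 50% | 0.25 | 0 | 212.50 | 0.1250 | 0 |

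First row: 5 × (0.09 − 0.25)/2 = −0.400, and −0.400/√(208.5 × 0.085) = −0.095. Swapping the groups reverses the sign. Prevalences of p and 1 − p, such as 70% v 30%, have equal variances and give zero.

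**Scale against sampling noise.** About 1,500 practices in three to six typologies plus control make four to seven groups: 1,500/7 ≈ 214 to 1,500/4 = 375 each, if equal. If the correlation were tested at 5% with 250 to 375 cross-strategy pairs, simulation gives these false rejection rates:
- 10% v 50%: about 33–35% at 250 and 45–46% at 375
- 20% v 50%: about 11–12% at 250 and 15–16% at 375
- 30% v 50%: about 6%
- equal prevalence: about 4%

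The article states no such test. The rates only show how visible the distortion would be.

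**A true moderator can be hidden or exaggerated.** Take prevalence 15% v 50% (V = 0.1275 and 0.25), s = 10 and a true slope difference of 5 points.
- Slopes 10 and 5: Cov = (10 × 0.1275 − 5 × 0.25)/2 = 0.0125, a correlation of about 0.003. The moderator disappears.
- Slopes 5 and 10: Cov = (5 × 0.1275 − 10 × 0.25)/2 = −0.931, a correlation of about −0.20. It is amplified.

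**Effect on weights.** Take two independent binary characteristics, each at 50% v 10%, with larger assumed slopes on the 0–1 scale and residual SD 0.15. The first has slope 0.10 in both groups. The second has slopes 0.05 and 0.139, a true interaction of −0.089. With 250 practices per group, the simulated pairwise weights average +0.099 for the first and −0.001 for the second, so the ranking is reversed. Coefficients from a model with group-by-moderator terms average +0.007 and −0.087 (simulation standard error about 0.004), close to the true 0 and −0.089.

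**The case against.** Much can be said for the plan.

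- **The article is condensed.** It summarises a cited method in one clause. A reader might infer that pairs may be formed without regard to strategy, or that the outcome is the ABCS level. The documents do not support that reading: the composite serves a comparison of strategies and extends the difference-in-differences model, so cross-strategy pairs and change scores are natural. The working assumes both, and nothing is claimed about their not being spelled out.
- **Not every candidate is prognostic for change.** Selection also draws on theory and qualitative findings, and an association with baseline ABCS level does not imply one with change. If candidates were screened by the three-way test, most purely prognostic ones would drop out. The text neither says nor excludes this. Screening would still leave the survivors weighted by the same rule.
- **Some contrasts may be balanced.** Cooperatives may use cluster-randomised or stepped-wedge designs, and intensity typologies may cut across Cooperatives. That would protect those contrasts, but pairing is not confined to them.
- **The imbalance is assumed.** This stands. No moderator distributions are given, and at 30% v 50% the distortion is negligible.
- **The hidden-moderator case is chosen near exact cancellation.** This stands too. It shows that a miss can happen, not that it is likely.
- **The composite is supplementary.** The individual three-way tests remain and could detect a moderator that the composite misses. They do not set its weights, however.

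**Conclusion.** The point holds in limited form. The stated criterion equals a measure of moderation only when the moderators' variances (jointly, their covariance matrices) match between the groups compared, or when they have no average association with change. The design does not secure the first, and the article does not establish the second. The composite can therefore credit prognostic-only characteristics, with either sign, and under-weight real moderators. Because this is a property of the quantity being maximised, larger samples and out-of-sample evaluation leave it in place.

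The size runs from nil to a correlation of about 0.10 under the assumed 5-point association and SD of 10, depending on an imbalance that cannot be read from the document. A reader might conclude that every prognostic variable will receive weight, or that the composite will generally fail. That goes too far: small imbalances do little harm, mean differences do none under linearity, and some contrasts may be randomised. The main difference-in-differences estimates and the individual moderator tests are unaffected.

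**What to change.** Take the weights from the model already planned. Fit the selected moderators jointly, with moderator-by-time and moderator-by-strategy-by-time terms, and use the three-way coefficients as the weights, one composite per strategy contrast. State the scale on which they are read, since the ABCS models are beta regressions.

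If the pairwise form is kept, either reweight practices first so that the moderators have the same distribution in both groups, or confine pairing to randomised contrasts. In either case, tabulate the moderators by strategy group so that the remaining imbalance can be seen.

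The cost is a change of wording and a little programming, with no new data. The composite may look weaker than under the pairwise rule. Reweighting costs precision where groups overlap poorly, and confining pairs to randomised contrasts reduces the number of practices used.

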#### Summative explanations for variation in outcomes across Cooperatives

To analyze why some intervention strategies are more effective than others, the ESCALATES team will analyze data among a group of high and low performing practices, using the same steps for qualitative data analysis described above. Data for this analysis will include fieldnotes, interviews, and external support/practice implementation tracking data which will allow us to establish what the practices implemented to improve ABCS delivery. Importantly, the qualitative team will be blinded to a practice’s status as a high or low performer during the data collection and analysis process. The qualitative team will identify mechanisms of practice change with regard to ABCS performance, the factors that influence a practice’s ability to implement or not implement change, and practice members’ experiences with their respective Cooperative’s intervention. At this stage, the qualitative team will bring in other data sources to make sense of the characteristics that distinguish practices. The end product will be a table of 40–60 practices and the factors or elements the qualitative team identifies as potentially important to practice change and improvement, and whether this element is present or absent for a practice. Next, the quantitative team will add practice performance to this table. A joint display will be created for a mixed methods analysis comparing the high and low performance practices in terms of qualitative findings and quantitative results. In order to distill a clear understanding of the factors associated with successful implementation, the qualitative team will use this information to conduct a deviant case analysis [72], examining in greater detail practices not conforming to our initial interpretation of what distinguishes low and high performing practices. As a final step, the full ESCALATES team will reflect on findings to fully identify the range of factors and characteristics vital to successful implementation of ABCS among which types of smaller practices and the key elements of external support required for practice improvement and for developing ongoing QI capacity.

### Trial status

The ESCALATES team has engaged the seven Cooperatives in the data harmonizing process, conducted one site visit with each Cooperative, and are working to refine a common set of measures and procedures for data collection. Cooperatives’ recruitment of practices is in progress. The start of baseline data collection and implementation of interventions will vary by Cooperative with start dates scheduled between January 2016 and April 2016.

